### Intervention description {11a}

#### Assessment procedure

After women with a history of recurrent SUI have been identified, standard assessments as per NICE NG123 guidance [4] will be undertaken, including urodynamic testing, to confirm diagnosis. These assessments will also help to ascertain what type of surgery would be suitable for the patient, should she be randomised to the “surgical” treatment arm. Following these assessments, the patient is then randomised (allocated) to either the endoscopic (bulking injections) or the surgical treatment arm and will receive their intervention according to usual local practice.

#### Surgical treatment arm

The type of surgical intervention received by participants who are randomised to the surgical treatment arm will be decided following a detailed discussion between the patient and their surgeon (clinician), as per usual local practice. The PURSUIT study will not impose a specific surgical procedure upon patients. Surgery options available for recurrent SUI are autologous fascial sling, colposuspension and AUS. Currently, there are specific rules from the NHS which regulate the use of mesh in vaginal surgery, including midurethral tapes. The rules relevant at the time will be used for anyone wishing to consider this type of surgery.

#### Endoscopic (bulking injections) treatment arm

Endoscopic urethral bulking agents to reduce the size of the channel (also known as bladder neck injections) are injected into the urethra wall under direct vision, using a cystoscope. Examples of urethral bulking agents are Bulkamid®, Deflux® and Macroplastique®. The PURSUIT trial does not impose which urethral bulking agent(s) should be used; sites should use their usual urethral bulking agent(s). In the endoscopic arm, repeat injections are permitted.

### Criteria for discontinuing or modifying allocated interventions {11b}

Participants can choose to withdraw for any reason, at any time, during their involvement in the trial. Participants can withdraw from complying with the allocated trial treatment or providing data to the trial without affecting their usual care. In both cases, efforts will be made to report the reason for withdrawal as thoroughly as possible in a study-specific form. If a participant wishes to withdraw from receiving the allocated trial treatment, efforts will be made to continue to obtain follow-up data, with the permission of the patient or family as appropriate (including access to medical notes/databases). In the event the clinician feels it is unsafe for the participant to continue in the study, he/she can withdraw the participant from the study.

If a delay has occurred between confirmation of eligibility and the delivery of the allocated intervention, site staff will ensure eligibility is still valid before proceeding. If the participant is no longer eligible, for example due to a change in symptoms, they would be withdrawn from the study.

There should be no cross-over of patients from their randomised treatment allocation to the alternative treatment until after the primary outcome is recorded (1 year post randomisation). However, this is guidance only and cannot be imposed.

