### Trial design {8}

A two-arm randomised controlled trial in women with recurrent stress urinary incontinence comparing endoscopic intervention (urethral bulking injections) with a surgical intervention (current NHS options) (Fig. 1, trial flowchart). The patient allocation ratio is 1:1.

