### Sample size {14}

To inform our calculations we reviewed the literature using the ICIQ-UI-SF. A recent study of women with SUI suggested that the minimum clinically important difference was −5 when using anchor-based methods, and −2 with distribution-based methods [18]. We felt that the conservative estimate of −2 (equivalent to a difference of 0.5 standard deviation (SD)) was an important difference. To allow for the possibility that 5% of women randomised to surgery instead receive endoscopic treatment before 1 year, we reduced difference to detect to −1.9. Thus we estimate that we need to recruit 250 women (125 in each treatment arm) to detect a difference in mean ICIQ-UI-SF at 1 year of 1.9 (assuming common SD of 4.1; in line with the assumptions made in the study by Sirls et al. [18]) with 90% power and a significance level of 5%. This includes an inflation factor accounting for 20% loss to follow-up, as we are using a PROM as the primary outcome.

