#### Randomisation

A local research nurse or trained delegate (or member of the central trial team) will randomise patients using the online or telephone randomisation system. Randomisation will only be done after eligibility has been confirmed, written consent obtained and the patient has had at least 24 h to consider the study information and had any questions answered. Randomisation can be conducted during a face-to-face consultation (clinical appointment or study-specific visit) or be completed remotely. Site staff will inform participants of their treatment allocation during or after the consultation. Once a participant has been randomised, they are ‘enrolled’ in the study, they will be added to the appropriate procedure waiting list (as per usual local clinical practice) and treatment (intervention delivery) can proceed. Site staff will notify the participant’s General Practitioner (GP) that their patient has entered the trial.

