### Plans to promote participant retention and complete follow-up {18b}

We will take active measures to minimise loss of women from the trial. Questionnaire completion will be followed up and managed by the central trial team using a central administrative database to notify the team when questionnaires are due. If a participant fails to return a questionnaire, a total of up to four reminders per time point (either telephone, email or postal) can be actioned by the site team or central trial team. In the case of a missing questionnaire, the response to the questionnaire can be collected from the participant over the telephone to reduce loss to follow-up. Multiple options are available to participants for them to complete their questionnaires, this ensures that the questionnaires are easily accessible to everyone (post/online/telephone). Other methods to promote participant retention will include obtaining back-up ‘best contact’ addresses, contacting the participant’s GP practice to check their contact details on record are still valid [24] and using ‘thank you’ vouchers as retention incentives [25]. In addition, we may access centrally held NHS data, for example via the NHS Strategic Tracing Service in England and Wales, to find new addresses.

If a participant withdraws/is withdrawn from the study, the study team would retain, confidentially, any data collected up to the point of withdrawal for analysis. As advised in the PIL, we will continue to collect data from a participant’s electronic records unless they request otherwise.

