## Statistical methods

### Statistical methods for primary and secondary outcomes {20a}

All analyses and reporting will be in line with CONSORT guidelines. Primary analyses will be performed on the intention-to-treat (ITT) basis, analysing women in the groups to which they were randomised. A full SAP will be developed and agreed by the TSC and DMC prior to undertaking analyses for the main trial and will be submitted as an update.

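### Women who lose eligibility between randomisation and treatment are withdrawn from the study, so their 1-year ICIQ-UI-SF is avoidably lost on grounds related to the outcome

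*Protocol article*

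**What the plan says.** Criteria for discontinuing or modifying allocated interventions {11b} covers delays between confirmation of eligibility and delivery of the allocated intervention. Sites re-check eligibility before proceeding, and: "If the participant is no longer eligible, for example due to a change in symptoms, they would be withdrawn from the study". The same section lets a clinician withdraw a woman from the study on safety grounds. For a woman who herself withdraws from the allocated treatment, however, it asks for efforts to go on obtaining follow-up data.

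Plans to promote participant retention and complete follow-up {18b} says that for anyone who withdraws or is withdrawn, "the study team would retain, confidentially, any data collected up to the point of withdrawal for analysis". Collection from electronic records continues unless she asks otherwise.

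Statistical methods {20a} states: "Primary analyses will be performed on the intention-to-treat (ITT) basis, analysing women in the groups to which they were randomised". Section {20c} bases the primary analysis on observed data, with imputation as a sensitivity analysis.

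**The concern.** The rule refers to the allocated intervention, so it operates after randomisation. The Randomisation section puts a woman on a procedure waiting list once she has been randomised, and the Discussion (Low surgical prioritisation of the patient group) reports waits above 1 year at many hospitals.

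The one trigger that the article names is a change in symptoms, which is close to what the ICIQ-UI-SF measures. Women removed this way are unlikely to be a random sample of their arm. The primary outcome is a questionnaire returned to the central team {18a}, so record collection after withdrawal cannot replace it.

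At stake are outcome data missing for a reason linked to the outcome, an intention-to-treat set reduced by a written rule, and some loss of power beyond what was budgeted. An analysis plan cannot recover questionnaires that were never sent.

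**Working it through.** **1. Does the rule reach randomised women?** Yes. {11b} runs up to delivery of the allocated intervention, and allocation exists only after randomisation. Implementation {16c} describes the pre-randomisation re-check under delayed randomisation separately, so {11b} is not confined to that period.

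**2. Is the primary outcome recoverable?** Not by any route the article describes. {18b} gives data up to withdrawal plus electronic records; {18a} makes the ICIQ-UI-SF a participant questionnaire.

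**3. Are like cases treated alike?** No. A randomised woman who withdraws from the allocated treatment is followed up; a randomised woman who loses eligibility before receiving it is withdrawn.

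**4. The plan's own sample size.** Inputs from Sample size {14} and Trial design {8}: 250 women, 125 per arm, "to detect a difference in mean ICIQ-UI-SF at 1 year of 1.9", "assuming common SD of 4.1", 90% power, 5% significance (two-sided assumed), 1:1 allocation, 20% loss.

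- n per arm = 2 × (1.960 + 1.282)² × 4.1² / 1.9² = 97.9, so 98.
- 98 / (1 − 0.20) = 122.5, so 123 per arm, 246 in total. The stated 250 reproduces and is not disputed.
- With 125 × 0.80 = 100 evaluable per arm, the standard error is 4.1 × √(2/100) = 0.580 and 1.9/0.580 = 3.28. Power = Φ(3.28 − 1.96) = 0.906 (0.903 from the t distribution).

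**5. Power if these withdrawals come on top of the 20%.** The documents give no rate, so this is an assumed range, equal in both arms and without credit for baseline adjustment.

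| Extra loss | Evaluable per arm | Power | Total N for 90% power |
|---|---|---|---|
| 0 | 125 × 0.80 = 100 | 0.906 | – |
| 5% | 125 × 0.75 = 93.75 | 0.887 | 262 |
| 10% | 125 × 0.70 = 87.5 | 0.865 | 280 |

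**6. Shift in the estimate.** If a share p of an arm is removed and their mean lies D points from the whole-arm mean, the retained mean moves by pD/(1 − p). The net shift is the difference between arms. The shares and D are assumptions, with D taken in the same direction in both arms and other losses taken as unrelated to outcome. D of 3–5 points is 0.7–1.2 of the planned SD.

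| Withdrawn, one arm vs other | D = 3 | D = 4 | D = 5 |
|---|---|---|---|
| 10% vs 3% (0.1111 − 0.0309 = 0.0802) | 0.24 | 0.32 | 0.40 |
| 10% vs 5% (0.1111 − 0.0526 = 0.0585) | 0.18 | 0.23 | 0.29 |

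Against 1.9 this is 9% to 21%. With equal shares and equal D the shift is zero. Steps 5 and 6 are separate scenarios.

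**The case against.** The strongest reply has five parts.

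- **Delayed randomisation.** {16c} and the Discussion (Treatment (intervention)) let sites hold back randomisation when waits are long and confirm eligibility first. This makes many re-checks harmless, because they fall before randomisation. It stands as a mitigation, but it is an option, aimed at pauses and considerable delays, and {11b} still governs any wait after randomisation.
- **Missing data are provided for.** {20c} has an imputation sensitivity analysis. That helps, but the primary analysis uses observed data, and withdrawal driven by symptoms makes missing at random harder to defend.
- **The trigger is wider than symptoms.** Eligibility can also be lost through pregnancy, prolapse or other criteria, and symptoms can change in either direction, so deviations may partly cancel. This is fair and is one reason the size cannot be fixed.
- **The article condenses a fuller protocol.** {18b} does not expressly say that questionnaires stop, and the full protocol may define levels of withdrawal. This too is fair: the loss of the questionnaire is the natural reading of {11b} and {18b} together, not an explicit statement.
- **The power loss may be smaller.** These women may fall within the 20% allowance, and adjusting for baseline ICIQ-UI-SF should recover some precision.

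A reader might go further and infer that withdrawals will differ by arm, or that the intention-to-treat analysis is invalidated. The documents support neither. They give no waits or withdrawal rates by arm, and the Discussion puts all incontinence procedures in the same lowest priority class. Lists specific to each procedure and unblinded site staff {17a} make a difference plausible, no more. Nobody is moved between groups either; the randomised comparison is depleted, not re-formed.

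**Conclusion.** The concern holds as one of avoidable, outcome-related missingness created by a written rule. Followed as written, {11b} with {18b} loses the 1-year ICIQ-UI-SF of randomised women who cease to be eligible. That sits badly with the aim in {20a} and with the follow-up {11b} gives to women who withdraw from treatment. This conclusion does not depend on any difference between arms.

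The size does depend on assumptions. Bias needs withdrawal shares or score gaps that differ by arm. At 10% against 3–5% withdrawn and scores 3–5 points from the arm mean, the shift is about 0.2–0.4 points against 1.9. If the losses are balanced and alike, there is no bias and the cost is power: about 87–89% instead of about 90% if 5–10% are lost beyond the planned 20%.

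**What to change.** Reconcile {11b}, {18b} and {20a} on outcome data. State that a woman who loses eligibility, or is withdrawn by a clinician, after randomisation remains in outcome follow-up, including the 1-year ICIQ-UI-SF, and is analysed in her randomised group unless she withdraws consent to follow-up. The change concerns data collection alone; whether such women receive treatment is a clinical matter on which nothing is proposed.

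The cost is a protocol amendment, with the steering committee, sponsor and ethics/HRA approvals that {25} describes for important amendments. The participant information leaflet may need updating, since {18b} ties data collection after withdrawal to it, and a few extra questionnaires must be sent. No additional recruitment is needed: if these women return their questionnaires, the rule adds no loss and the planned 250 stands.

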### Strategies to improve adherence to interventions {11c}

Study sites are asked to monitor and record all treatments that a participant receives; if cross-over of patients from their randomised treatment allocation to the alternative treatment arm does occur, then details, including reason(s) why, will be recorded in the study-specific case report forms.

### Relevant concomitant care permitted or prohibited during the trial {11d}

Participants will receive all standard care required during their participation in the trial, as per usual clinical practice.

### Provisions for post-trial care {30}

The interventions offered in this trial (both the operations in the surgery arm, and the bulking injections in the endoscopic arm) are part of standard NHS care. Accordingly, the patients will continue with the NHS standard care for their condition after the end of the research.

### Outcomes {12}

#### Primary outcome measure

The primary outcome is the patient-reported outcome measure (PROM) of continence using the International Consultation on Incontinence Questionnaire - Urinary Incontinence - Short Form (ICIQ-UI-SF) at 1 year after randomisation.

#### Secondary outcome measures

Longer term clinical subjective measure of continence at 6 months and 2 and 3 years post randomisation (ICIQ-UI-SF)Improvement of symptoms post-intervention at 1, 2 and 3 years post randomisation (Patient Global Impression of Improvement (PGI-I) questionnaire)Procedure/operative assessment measures collected at the time of intervention and at 6 months post intervention: procedure/operation time, estimated blood loss, hospital stay, return to normal activityAssessment of sexual health at 1, 2 and 3 years post randomisation (Pelvic Organ Prolapse/Urinary Incontinence Sexual Questionnaire-IUGA Revised (PISQ-IR))The safety of each intervention (adverse events, AE) and the likelihood of re-treatment assessed at intervention, 6 months post intervention and 6 months and 1, 2 and 3 years post randomisationCost-effectiveness from NHS and societal perspectives at 1 year post randomisation in terms of quality-adjusted life years (QALYs) and ICIQ-UI-SF at 1 year, and from a secondary care perspective in terms of QALYs at 3 years post randomisation. QALYs to be calculated from the EuroQol 5-Dimension 5-Level (EQ-5D-5L). Secondary care resource use to be abstracted from Trust electronic systems (or HES) at 1 and 3 years post randomisation, other resource use to be collected by questionnaires at 6 months and 1year post randomisation.Patient experiences of the intervention at 6 months and 1 year and 3 years post intervention (qualitative interviews with patients)Clinician views of the intervention at, or around, baseline (qualitative interviews with clinicians)

### Participant timeline {13}

The participant timeline is shown in Table 1.

**Table 1 Tab1:** Participant timeline

	Pre-baseline	Baseline	Treatment	Post-treatment				Post-randomisation			
				3–6 months	6 months	1 year	3 years	6 months	1 year	2 years	3 years
**Pre-screening and eligibility**	X										
**Informed consent**		X									
**Randomisation**		X									
**Interventions**			X								
**Data collected by site staff**											
- Case report forms		X	X		X			X	X	X	X
- Adverse events			X		X			X	X	X	X
**Participant Questionnaires**											
- ICIQ-UI-SF		X						X	X	X	X
- PISQ-IR		X							X	X	X
- EQ-5D-5L		X						X	X	X	X
- PGI-I									X	X	X
- Non secondary care resource use								X	X		
**Secondary care resource use**									X		X
**Interview Study**											
- Qualitative interview (patients)		X		X		X	X				
- Qualitative interview (staff)		X									

### Sample size {14}

To inform our calculations we reviewed the literature using the ICIQ-UI-SF. A recent study of women with SUI suggested that the minimum clinically important difference was −5 when using anchor-based methods, and −2 with distribution-based methods [18]. We felt that the conservative estimate of −2 (equivalent to a difference of 0.5 standard deviation (SD)) was an important difference. To allow for the possibility that 5% of women randomised to surgery instead receive endoscopic treatment before 1 year, we reduced difference to detect to −1.9. Thus we estimate that we need to recruit 250 women (125 in each treatment arm) to detect a difference in mean ICIQ-UI-SF at 1 year of 1.9 (assuming common SD of 4.1; in line with the assumptions made in the study by Sirls et al. [18]) with 90% power and a significance level of 5%. This includes an inflation factor accounting for 20% loss to follow-up, as we are using a PROM as the primary outcome.

### Recruitment {15}

Participants will be recruited initially from 20 NHS urology and urogynaecology referral units in UK hospitals. If necessary, to reach the target sample size, the study will be opened at more referral units.

Assignment of interventions: allocation

### Sequence generation {16a}

The randomisation sequence will be generated by the BTC using their established (proven) online randomisation system or automated telephone system. Patients will be randomised on a 1:1 basis to the “endoscopic” or “surgical” intervention (treatment) arm. The individual randomisation will be stratified by site.

### Concealment mechanism {16b}

Site staff will only inform participants of their allocated intervention after the participant has completed and returned their baseline questionnaire to ensure responses are not biased by the patient’s knowledge of their allocation.

### Implementation {16c}

If study interventions are proceeding as usual (according to routine clinical pathways and timings), randomisation and data collection will be done when informed consent is obtained. If delivery of study interventions is paused, or there are considerable delays, due to the COVID-19 pandemic, patients may provide informed consent to take part, but randomisation and baseline data collection will not be undertaken until treatment interventions can proceed. As soon as treatment interventions can proceed, site staff will ensure eligibility and consent are still applicable and valid before conducting randomisation and collecting baseline data. Previous urodynamic results (used for initial confirmation of study eligibility) can be used providing that the doctor considers that they are still relevant, i.e. the tests were conducted since the woman’s last procedure and her symptoms have not changed since then.

#### Randomisation

A local research nurse or trained delegate (or member of the central trial team) will randomise patients using the online or telephone randomisation system. Randomisation will only be done after eligibility has been confirmed, written consent obtained and the patient has had at least 24 h to consider the study information and had any questions answered. Randomisation can be conducted during a face-to-face consultation (clinical appointment or study-specific visit) or be completed remotely. Site staff will inform participants of their treatment allocation during or after the consultation. Once a participant has been randomised, they are ‘enrolled’ in the study, they will be added to the appropriate procedure waiting list (as per usual local clinical practice) and treatment (intervention delivery) can proceed. Site staff will notify the participant’s General Practitioner (GP) that their patient has entered the trial.

### Assignment of interventions: blinding

#### Who will be blinded {17a}

Due to the nature of the interventions, participants and those administering the interventions will not be blinded to group allocation nor will the supporting clinical and site staff, to ensure relevant data collection. Two statisticians based at the UOB will support this trial. The senior statistician co-applicant will be blinded throughout the trial. The second trial statistician will perform all disaggregated analyses according to a pre-specified statistical analysis plan (SAP) and will attend closed Data Monitoring Committee (DMC) meetings as required. The health economist(s) will be blinded when cleaning data, but unblinded when conducting the analysis. Other members of the study team will remain blinded to aggregate data. The Study Manager and administrative staff will likely be unblinded to individual-level data to enable appropriate data collection.

